#### Service use

Hospital admission and length of stay will be used as intermediate outcome measures to assess how the PACT model affects hospital utilisation.

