**Methods/design:**

This is a prospective, non-randomised matched control before-and-after intervention study. Patients in the intervention group will be recruited from the hospital sites that have implemented the PACT model. The controls will be recruited from two hospitals without the model. The control patients and the index patients will be matched according to sex, age and number of long-term conditions. The study aims to include 600 patients in each group, which will provide sufficient power to detect a clinical change in the primary outcome. The primary outcome is the physical dimension of the Short Form Health Survey (SF-36). Secondary outcomes are the Patient Generated Index (PGI), the Patient Activation Measure (PAM), the Patient Assessment of Chronic Illness Care (PACIC), hospitalisation and length of stay. The cost-effectiveness study takes a health provider perspective and calculates the cost per quality-adjusted life-years (QALYs) gained. The data will be collected at baseline, 6 and 12 months. The data will be analysed using techniques and models that recognise the lack of randomisation and the correlation of cost and effect data.

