#### Status

At the time of writing, all team members, including a part-time recording secretary, have been appointed at the hospital in Tromsø. The test and developing phase is well underway. The team is now actively promoting their existence and services by visiting GPs, district nurses, other community service providers and hospital wards and clinics. The first patients have been referred to the team as part of the test phase, but no patients have yet been enrolled in the trial. The team has been assigned office space at the hospital and has scheduled two daily meetings to plan activities and discuss patients. In between team meetings, the team is conducting home visits, attending coordination meetings, writing case reports and updating patient records. The second hospital has finished the planning phase and will be operational by fall 2015.

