### Design

This evaluation study is a prospective non-randomized, matched control, before-and-after study [28]. We will compare all hospitalised patients meeting the inclusion criteria with patients receiving usual care in a control setting. The PACT model is directed at the organisational level or geographic site, affecting all patients within the uptake area. Therefore, the intervention and controls are separated in different hospitals to avoid contamination. The chosen design improves comparability between the patient populations by matching them on factors known to be important for outcomes (age, sex and number of conditions), adjusting for baseline differences between the populations with a before-after design and adjusting for known confounders by the propensity score method [29, 30].

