### Participants

The intervention group participants will be recruited consecutively until we have reached the target of 600 patients. As soon as the patients have signed the consent form, the intervention will start and the baseline data collection will begin. The follow-up period will be one year from the initial assessment for each patient.Inclusion criteria: Patients with emergency admission to the UNN internal medicine department in Tromsø and Harstad who are over the age of 65 years, have two or more long-term conditions and provide valid written informed consent (either by the patient or the next of kin).Exclusion criteria: Language barriers, life expectancy of less than three months and unable to provide written informed consent.

The control population will be recruited from the Nordland Hospital in Bodø and from the hospital UNN Narvik. When an index patient is identified in the hospitals using patient-centred teams, at least two eligible patients from the control hospitals will be identified. Sex, age and number of long-term conditions will be used to match the control patients to the index patients. The control patients will be subject to the same data collection as the intervention patients.

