Dedicated, interdisciplinary patient-centred teams can be a new, more effective and cost-effective way to provide health care to older patients with long-term complex needs. Recent studies and reviews underpin the importance of strategies that support patient involvement, engagement and self-care [57–59]. The active two-way patient–provider dialogues and practical skill development in self-management are reported to be important for better outcomes [60]. The patient-centred teams will ensure that several elements of self-management, such as goal setting, self-monitoring and care plans, will be realised, thereby providing more insights into the relevance of self-management in terms of outcomes and cost effectiveness. In the United Kingdom, the transformation from conventional to patient-centred care in the health system has been estimated to have a cost-cutting potential of 7 % [61].

The strengths of the present study are its real world setting and the involvement of designated health professionals in designing and developing the integrated care model. The PACT model has been initiated and is solely driven by managers and clinical personnel at the hospital and the community services. The structure and organisation of the team and how they work will be continuously adapted to the clinical and everyday routines at the hospitals and in the home care settings. This might increase the probability of sustaining the PACT model after the project has ended.

The main limitation of the study is the lack of randomisation. Although we recognise that randomisation is the most robust method of avoiding systematic bias between comparison groups, this method is not possible in this trial. The PACT model aims to improve geriatric care in terms of both structures and routines at the organisational level of two hospitals. A patient-level randomisation, which requires the organisation to switch between old “usual care” and a new team-based proactive care, is unlikely to be successful [56]. Randomising the organisations could be an alternative, but with only four hospitals, this is too small to make cluster randomisation meaningful. We are therefore using a matched control group with before-and-after comparisons. This design is approved by Cochrane for use in systematic reviews of interventions “*that cannot be randomized, or which are extremely unlikely to be studied in randomized trials*” [28].

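### The before-and-after comparison is not carried through to admissions and length of stay, so standing differences between the hospitals may be read as PACT effects (RQ3)

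*Protocol article*

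**What the plan says.** All places are in the Protocol article.

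- **Role of the before-and-after element.** The Design section lists, among the features that improve comparability, "adjusting for baseline differences between the populations with a before-after design". The Discussion explains why neither patients nor hospitals can be randomised and continues: "We are therefore using a matched control group with before-and-after comparisons".
- **What the before is.** The abstract states: "Patients in the intervention group will be recruited from the hospital sites that have implemented the PACT model". Under Participants: "As soon as the patients have signed the consent form, the intervention will start and the baseline data collection will begin". Under Status, for Tromsø: "The first patients have been referred to the team as part of the test phase, but no patients have yet been enrolled in the trial". No earlier period or cohort is described at Tromsø, Harstad, Bodø or Narvik.
- **Outcomes.** Outcome measures defines the primary SF-36 outcome as an adjusted difference in change. Service use gives one sentence: "Hospital admission and length of stay will be used as intermediate outcome measures to assess how the PACT model affects hospital utilisation". It mentions no change from a prior period. Data collection and management takes hospital use from hospital records and states no time window.
- **Adjustment.** Matching is on age, sex and the count of long-term conditions. The Analyses section builds a score for change in quality of life, with patient characteristics as its examples. It then says that within a stratum the teams are the one known respect in which patients differ, and likens this to randomisation. Baseline resource use appears in that section only as an input to multiple imputation.

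**The concern.** RQ3 asks whether PACT reduces unplanned admissions and length of stay. The comparison sets Tromsø and Harstad against Bodø and Narvik. Hospitals can differ for years in admission thresholds, bed supply and discharge practice, whatever patients they treat. The usual protection is a measurement from before the new service opened, and the article invokes a before-and-after design. For hospital use, however, no before-value is assigned.

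Preventing admissions is a stated aim of PACT, and the article says the results will inform decisions on continued funding and expansion. Inpatient use is also a cost component in the economic evaluation, so a bias here carries over into it.

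**Working it through.** **1. The plan's own figure.** The only power statement is for SF-36: 4 points, SD 25, alpha 0.05 (two-sided assumed), 600 per group, power 0.80.

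- n = 2 × (1.960 + 0.842)² × 25² / 4² = 614 per group, against 600 stated.
- Power at 600: SE = 25 × √(2/600) = 1.443; 4/1.443 = 2.771; Φ(2.771 − 1.960) = 0.79.

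That figure reproduces. None is given for admissions or length of stay.

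**2. Which outcome has a before-value.**

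| Outcome | Before-value in the article |
|---|---|
| SF-36 (primary) | Baseline questionnaire; outcome is a difference in change |
| Admissions in follow-up | None assigned; one could come from records before consent |
| Length of the index stay | None possible for the same patient |

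**3. Why patient-level adjustment is not enough.** Write the expected follow-up outcome as a patient part, plus a hospital part, plus the PACT effect θ. Matching or stratifying on patient characteristics can at best balance the patient part. The contrast then estimates θ + (mean hospital part at the PACT hospitals − mean hospital part at the controls). A hospital term cannot separate the two, because PACT does not vary within a hospital. So within any stratum the hospital always differs as well as the team.

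**4. How much a standing gap could matter.** The article gives no readmission rate, length-of-stay SD or between-hospital gap, so everything below is assumed. Set θ = 0, with 600 per group and a two-sided 5% test. With gap d, the chance of a significant result is Φ(d/SE − 1.96) + Φ(−d/SE − 1.96).

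- *Readmission proportion near 30%:* SE ≈ √(2 × 0.3 × 0.7/600) = 0.0265. Gaps of 2, 3, 5 and 8 points give 12%, 21%, 47% and 86%. For a 5-point gap, base rates of 20% to 40% give 58% to 43%.
- *Length of stay:* SE = SD × √(2/600), which is 0.289 for SD 5 and 0.404 for SD 7. A 0.5-day gap gives 41% or 24%; a 1-day gap gives 93% or 70%.
- *Admission rate:* SE(log RR) = √(2(1/μ + k)/600). For μ of 0.8 to 1.2 per patient-year and negative-binomial dispersion k of 0.5 to 1.5, this is 0.067 to 0.096. Using Φ(|ln RR|/SE − 1.96), a standing rate ratio of 0.90 gives 20% to 35%, and 0.85 gives 40% to 68%.

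A gap in the other direction would hide or reverse a true benefit to the same degree.

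**5. What before-data would do.**

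- *Difference in differences:* a gap that is stable over time cancels. With independent before samples of equal size, the SE is multiplied by √2 = 1.41. At 30% and 600 per group, the difference detectable with 80% power goes from 2.802 × 0.0265 = 7.4 points to 7.4 × 1.41 = 10.5 points.
- *A participant's own prior use as a covariate:* in a linear model with equal variances and within-patient correlation ρ, the SE is multiplied by √(1 − ρ²), which is 0.95 at ρ = 0.3 and 0.87 at ρ = 0.5. It removes only the fraction ρ of a stable gap, so 70% or 50% would remain. It helps, but does not replace a before period.

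**The case against.** **Before-data are not absent.** A reader might infer that the study has no before information on hospital use at all, because everyone enters after PACT has opened. The documents do not support that. Baseline resource use is a named variable, the record extract has no stated window, and a patient enrolled after PACT opened still has an admission history before consent. What stands is narrower: that information is not assigned to RQ3, and for the index stay it cannot exist.

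**The article is condensed.** The model for a secondary outcome may be set out in a full protocol or analysis plan. That is a fair reply on the choice of covariates. It is weaker for a pre-PACT cohort, which is a matter of design and data access, and it does not excuse the sentence in Analyses about the only known difference, which is incorrect as printed.

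**The limitation is disclosed.** The Discussion names the lack of randomisation as the main limitation, and the Design section speaks of differences between populations, which can be read as patients only. Hospital-specific estimates and modelling of variation between centres are planned in the economic evaluation. The disclosure stands, but the before-and-after comparison is offered as the response to it. Hospital-specific estimates do not separate PACT from hospital either.

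**The magnitudes are assumed.** This is correct. They show what a gap of a given size would do, not that one exists. Nor do the roughly 9500 admissions in 2014, given under Sample size, tell how precise a before period would be. They are all medical emergency admissions at age 67 and over, are not restricted to two or more conditions, and are not split by hospital.

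**Conclusion.** The point holds in this form. For RQ3 the article neither describes a pre-PACT period nor assigns a before-value, so the before-and-after adjustment is unspecified for admissions and impossible within patients for the index stay. Since PACT coincides with hospital, two against two, standing differences in practice may enter the estimated effect in either direction. The statement in Analyses that the teams are the only known difference within strata is not correct.

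The size is not known from the documents. The range of 12% to 47% rests on an assumed 30% readmission proportion and assumed gaps of 2 to 5 points.

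A reader might go further and conclude that an RQ3 effect would be an artefact, or that hospital use dominates the cost result. Neither follows: no between-hospital gap is reported, and the article lists cost components without their sizes. The sample size for the primary outcome is not affected. This is a change worth making for a secondary question, not a fault that invalidates the study.

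**What to change.** 1. **Adjust for prior use.** In the RQ3 models, adjust each participant's admissions and bed-days for their own hospital use in the 12 months before the index admission, taken from the hospital records already drawn on. The cost is a defined extraction window and one covariate. As shown above, it removes only part of a standing gap.

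2. **Add a supporting difference in differences.** From records at all four hospitals, compare all eligible emergency medical admissions (over 65, two or more long-term conditions) before and after PACT opened. Use the same eligibility rule and no selection by consent in both periods; setting an unselected before cohort against consented participants would bring in a new bias. End the before period ahead of the first test-phase referrals. The costs are:
   - ethics approval for the extract, since the approval described under Ethics for electronic records is for identifying potential controls to invite;
   - lower precision, with an SE about 1.4 times larger for equal-sized independent before samples;
   - reliance on parallel trends;
   - hospital-by-period variation, which four hospitals cannot average out.

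   The analysis serves record-based outcomes only.

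3. **Correct the text.** Replace the statement in Analyses about the only known difference within strata with one saying that the design adjusts for patients' baseline differences and not for differences between hospitals. This costs nothing.

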#### Analyses

The analyses will use an intention-to-treat approach that includes all participants who signed the informed consent at the intervention and control hospitals. Missing data will be imputed using multiple imputations [48]. The multiple imputation model will include predictors from all time points, including health-related quality of life (SF-36), background variables, trial-related variables and resource use at baseline. Results with and without imputed data will be reported. The data will be analysed as a synthetic randomised controlled trial (RCT), using the propensity score method. This method postulates that each patient has a basic probability of the outcome of interest based on his/her characteristics [29]. Based on available knowledge for each patient (e.g. age, sex, education, ethnicity), we can calculate the patient’s propensity for the outcome (i.e. change in QoL). In subsequent analyses, we stratify analyses by this score. Within each stratum, the only known difference between patients with respect to the outcome will be the patient-centred teams. The fundamental requirement for validity in a causal analysis is that the variables used to create the propensity score are independent of the probability of getting the intervention. In common-sense terms, this means that in the synthetic study, within the same propensity score strata, the assignment to treatment is essentially the same as if it had been done by randomisation.

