### Data collection and management

Each hospital will have a part-time study nurse based in the geriatric department. The study nurses will administer the consent forms and support the data collection from the patients. The background variables and all the questionnaires will be completed by the patients at baseline, 6 and 12 months.

All data on health service use, including medication, will be collected from electronic information systems. Data on hospital use (hospital admission, length of stay, outpatient consultation, emergencies and medication) will be collected from the hospital records. Data on primary health resource use will be collected from the GPs, the municipalities and other available information systems. Data from the municipalities will supplemented by interviews with the providers. The cost associated with the PACT model itself will be determined by interviewing the PACT members (staff) and reviewing budgets.

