### Cost-effectiveness evaluation

#### Trial-based economic evaluation

The trial-based economic evaluation consists of a cost-utility analysis with a time horizon of 12 months. The analysis takes a health provider perspective and collects data on health resource use and health outcomes measured in quality-adjusted life-years (QALYs). The economic evaluation will be conducted in accordance with the CHEERS statement [49].

For the economic evaluation, health outcomes will be measured using the SF-6D instrument [50]. The SF-6D will be extracted from the SF-36 and will include physical functioning, role participation (combined role-physical and role-emotional), social functioning, bodily pain, mental health and vitality. The algorithm by Brazier et al. will be used to transform the scores into utility values [51]. The SF-6D scores will be transformed to QALYs by weighing the per-period estimates of utility scores with the time spent in the particular health state, assuming a linear change in utility over time. Imbalances in baseline values will be adjusted for using multiple regression [52].

Only health care costs assumed to be affected by the PACT model and of potential economic significance will be included in the main analysis. Costs borne by patients and productivity losses to society are considered less relevant for the patient group in this study. Two main cost components will be included: the costs related to the PACT model (technology and personnel costs) and the cost related to health services use over the course of the trial (hospital inpatient, outpatient, day hospital and emergency services, community-based health care services and medication). Cost weights will be applied to calculate the costs associated with each primary and secondary health resource activity. These will be collected from hospital accounting databases, national tariffs and official wage and price lists.

The cost-utility analysis will be based on the net-monetary benefit framework (NMB). The NMB approach allows for modelling the variability in the cost effectiveness between the centres and GPs [53]. NMB regression will be used to analyse whether the PACT model is more cost effective for a specific subgroup of patients (the effect modification in RQ 5).

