The data will be analysed using appropriate techniques that account for the correlation between cost and effect data. Trial-wide costs, QALYs and incremental cost-effectiveness ratios will be reported, as will hospital-specific estimates. If the economic evaluation finds that one option ‘dominates’ the other with a negative incremental costs (costs less) and a positive incremental effect (produces more QALYs), this will considered the most cost-effective option. If better outcomes are associated with higher costs, an incremental cost effectiveness ratio (ICER) will be calculated [54]. Cost effectiveness will then be assessed based on different willingness-to-pay (WTP) thresholds.

Sampling uncertainty will be handled through the use of p-values and confidence intervals (CIs) for costs, QALYs and incremental cost-effectiveness ratios. Confidence intervals for the mean differences in costs and effects between groups will be calculated using non-parametric bootstrap simulation. Cost-effect pairs will be plotted in the cost-effectiveness plane and show the 95 % confidence regions for the ratio. A range of different thresholds will be analysed using a cost-effectiveness acceptability curve.

Non-sampling uncertainty will be handled in sensitivity analyses. The most uncertain methodological assumptions will be varied to illustrate the robustness of the results. Sensitivity analyses will be performed on perspective (societal versus health provider) and different willingness-to-pay values.

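### The imputation model names resource use at baseline only; record-based follow-up use should be added, chiefly to protect the cost-effect correlation

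*Protocol article*

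**What the plan says.** The Analyses section of the protocol article states: "Missing data will be imputed using multiple imputations". It then describes the model: "The multiple imputation model will include predictors from all time points, including health-related quality of life (SF-36"), followed by "background variables, trial-related variables and resource use at baseline". Baseline is the only time point attached to resource use. The section adds: "Results with and without imputed data will be reported".

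Three other statements bear on this.

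- Data collection and management: for SF-36 and the other instruments, "all the questionnaires will be completed by the patients at baseline, 6 and 12 months". For service use, "All data on health service use, including medication, will be collected from electronic information systems".
- Trial-based economic evaluation: one of the two cost components is "the cost related to health services use over the course of the trial". QALYs come from the SF-6D, which is derived from the same SF-36 forms.
- The same section commits to "appropriate techniques that account for the correlation between cost and effect data".

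**The concern.** The two kinds of follow-up data have different sources. SF-36 depends on a frail patient returning a form; service use depends on records. When a 6- or 12-month form is missing, the patient's admissions over the same months will often still be known. They are among the few follow-up facts available about that patient.

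An imputation model without that information draws the missing SF-36 as if it were independent of follow-up use, given the remaining predictors. Two things are then at stake. First, the completed data understate the link between cost and QALY that the economic analysis is meant to respect. Second, if use is related both to health and to the chance of a missing form, the imputed scores are shifted, because missing-at-random holds only once use is in the model.

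**Working it through.** **The plan's own figure.** The article gives no figure for missing data. Its only relevant number is the power statement: 600 per group, SD about 25, difference 4, alpha 0.05 (two-sided assumed). The standard error is 25 x sqrt(2/600) = 1.443, and power = Phi(4/1.443 - 1.96) = Phi(0.811) = 0.791. This agrees with the stated 0.80, so 4 points and SD 25 serve as the yardstick. Everything else below is an assumption, because the article states no missingness rate, mechanism or use-health relation.

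**Step 1: correlation.** Suppose a fraction m of follow-up SF-36 is imputed without follow-up use. Observed pairs keep the true correlation r; imputed pairs keep only the part carried by the baseline predictors, r_b. When missingness is unrelated to use,

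r_completed = (1 - m) r + m r_b.

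In a simulation (n = 400,000) with baseline SF-36, baseline use and group as predictors, r_b was about -0.135.

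| Partial r | True r | m | Formula | Simulated |
|---|---|---|---|---|
| -0.2 | -0.278 | 20% | 0.8(-0.278) + 0.2(-0.135) = -0.249 | -0.248 |
| -0.2 | -0.277 | 40% | 0.6(-0.277) + 0.4(-0.135) = -0.220 | -0.221 |
| -0.4 | -0.421 | 20% | 0.8(-0.421) + 0.2(-0.135) = -0.364 | -0.361 to -0.366 |
| -0.4 | -0.421 | 40% | 0.6(-0.421) + 0.4(-0.135) = -0.307 | -0.303 to -0.307 |

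The attenuation was much the same whether heavier users, lighter users or neither were missing more often. It vanished only when the partial correlation was zero. Adding follow-up use restored the true value.

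**Step 2: what this does to net monetary benefit.** Var(NMB) = L^2 Var(Q) + Var(C) - 2 L Cov(Q,C), with L the willingness to pay. The relative effect of a change in correlation is greatest when L SD(Q) = SD(C), where the variance is proportional to 1 - r. Taking the SF-36 correlation as a stand-in for the cost-QALY correlation:

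- -0.42 to -0.30: sqrt(1.30/1.42) = 0.957, a standard error about 4% too small.
- -0.28 to -0.25: sqrt(1.25/1.28) = 0.988, about 1% too small.

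**Step 3: direction of bias in imputed SF-36.** In the Step 1 simulation, with log-odds of a missing form changing by 0.5 per SD of use, the bias in the imputed values was:

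- heavier users missing more often: +1.6 to +1.8 points (partial r -0.2) or +3.3 to +3.5 (partial r -0.4);
- missingness unrelated to use: about 0;
- lighter users missing more often: -1.5 to -1.8 or -3.3 to -3.4.

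Bias in the overall mean is m times these values, for example 0.4 x 3.37 = 1.35. With the same mechanism in both groups, bias in the between-group difference was within about 0.13 points of zero, which is simulation noise.

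**Step 4: primary contrast when response differs by group.** Set-up in SD units: SF-36 at 6 and 12 months = 0.5 x baseline SF-36 - b x follow-up use + residual, with half the residual variance shared between visits. The correlation of use with baseline SF-36 is -0.3. Logit P(12-month form missing) = a + c x use, with a set to give 30% missing in one group and 14% in the other. Imputation is by group, without follow-up use; results are multiplied by 25. Version A has baseline use as a predictor, correlated 0.5 with follow-up use. Version B gives baseline use no information. Entries are between-group bias in points for b = 0.2 / 0.3 / 0.4.

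| 6-month SF-36 | c | A | B |
|---|---|---|---|
| observed | 0.5 | 0.13 / 0.17 / 0.22 | 0.17 / 0.23 / 0.24 |
| observed | 1 | 0.23 / 0.35 / 0.40 | 0.28 / 0.42 / 0.49 |
| missing | 0.5 | 0.25 / 0.45 / 0.57 | 0.37 / 0.51 / 0.68 |
| missing | 1 | 0.49 / 0.72 / 0.99 | 0.60 / 0.91 / 1.16 |

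For example, in A with c = 1, b = 0.4 and no 6-month score, the group means are 1.92 and 0.93 points too high, and 1.92 - 0.93 = 0.99. Version A is closer to the plan, which names baseline use. With follow-up use added, the group-mean bias was within 0.02 points of zero.

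**The case against.** **The list is open.** The sentence begins with predictors from every time point and uses an inclusive list, so follow-up use is not ruled out. This stands: the wording is ambiguous, and to say that the plan excludes follow-up use would go too far. But the authors attached a time point to resource use, and that time point is baseline.

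**The 6-month score is in the model.** This stands and matters. SF-36 from all visits is named, and an observed 6-month score roughly halves the bias in the primary contrast. Patients who miss both follow-up forms get no such help.

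**A reader might infer that imputed SF-36 is biased upwards, or that the primary result is.** The documents do not support either as fact. They give no rate or direction of missingness; the bias can be zero or downward, and a shift common to both groups cancels in the between-group difference.

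**A reader might infer that imputed QALYs would be unrelated to cost.** They would not: the baseline predictors, and any 6-month score, still carry part of the relation. The effect is attenuation.

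**The plan has safeguards, and details belong in the SAP.** Results with and without imputation are promised. However, an analysis of returned forms does not use follow-up use either, so agreement between the two would not be reassuring. Techniques that model the cost-effect correlation can only work on the correlation left in the completed data. The functional form of the cost variables is indeed SAP detail, but the time point named for resource use is the article's own statement.

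**Follow-up use is affected by the intervention.** That would argue against adjusting for it in the outcome model. It is no reason to keep it out of the imputation model.

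**Conclusion.** The point holds as an improvement to an ambiguous sentence. The firm part is the attenuation of the cost-effect correlation, which needs only that use and health are related given the other predictors. Its effect on the NMB standard error is modest, about 1% to 4% in the scenarios of Step 2.

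The effect on the primary outcome is conditional: it needs missingness, or the use-health relation, to differ between the groups. That is possible with non-randomised groups in different hospitals, but the article does not state it. With SD 25, use effects of 0.2-0.4 SD, log-odds of 0.5-1 per SD of use and 30% v 14% missing, the bias is about 0.1 to 0.4 points when the 6-month SF-36 is observed (at most a tenth of the 4-point target). It is up to about 0.9 to 1.0 when it is not (about a quarter). If baseline use says nothing about follow-up use, the upper ends become 0.5 and 1.2. These figures concern missing forms and do not address how deaths are handled.

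**What to change.** Reword the sentence so that the imputation model includes record-based hospital and primary-care use or cost over 0-6 and 6-12 months, in addition to baseline use and SF-36 at all visits. State that the same imputed data sets serve the effectiveness and cost-utility analyses. Primary-care data may themselves be incomplete, since they come from several sources and the municipal data are supplemented by interviews; those variables can be imputed within the same model.

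The cost is one sentence. The data are already planned for collection, and the sample size is unaffected.
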